### Sample size

To estimate our sample size calculated for the primary effectiveness outcome, we used data from published literature to estimate the baseline prevalence of hypertension treatment (20%) and control (10%) rates in the Federal Capital Territory, Nigeria [25]. We based the anticipated effect on similar programs, including the KPNC Hypertension Control Program [2]. The power and sample size were estimated under a variety of conditions through Monte-Carlo simulation in SAS (v9.4, SAS Inc, Cary, North Carolina). Accounting for 10 sites dropping out, we estimated that 1200 patient visits per month across 50 sites over 9 months of baseline and 39 months of intervention would provide >80% power to detect a difference in treatment slope of 0.57% per month compared to underlying trend of 0.10% per month, resulting in hypertension treatment rate of 42.5% at the end of 48 months. Similarly, with the same sample size, we would have >80% power to detect a difference in control slope of 0.44% per month compared to underlying trend of 0.05% per month, resulting in hypertension control rate of 27.0% at the end of 48 months.

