### Timeline

During the formative phase of the study (April 2019 to August 2019), baseline qualitative assessments (i.e., key informant interviews and focus group discussions) were held with patients, health workers, and administrators to inform adaptation of the implementation package [17]. The control phase of the study included 11 months (January 2020 to November 2020) of sequential registration and empanelment of hypertensive patients at participating primary healthcare centers (Fig. 2). The intervention phase includes implementation of the remainder of the package components and evaluation over the subsequent 37 months (December 2020 to December 2023). Analysis and dissemination of baseline results occurred following conclusion of the control period [18]. Midway through the intervention phase, an additional component of CHEW-led home blood pressure monitoring and health coaching was introduced within a subset of 10 participating primary healthcare centers. Recruitment and follow-up of these patients will be carried out from September 2022 to February 2023.

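### The sample-size section labels 0.57 and 0.44 %/month as slope differences, but its end rates fit only if they are total intervention-phase slopes, and it powers 9+39 months where the trial runs 11+37

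*Protocol article*

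**What the plan says.** The Primary outcomes section makes the change in slope from the baseline slope, for monthly treatment and control rates, the co-primary effectiveness outcome.

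The Sample size section starts from a "baseline prevalence of hypertension treatment (20%) and control (10%) rates" taken from the literature. It assumes "1200 patient visits per month across 50 sites over 9 months of baseline and 39 months of intervention". For treatment it claims more than 80% power for "a difference in treatment slope of 0.57% per month compared to underlying trend of 0.10% per month", and it puts the month-48 treatment rate under this scenario at 42.5%. For control it claims the same power for "a difference in control slope of 0.44% per month compared to underlying trend of 0.05% per month", ending at 27.0% at the same time point.

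The Timeline section gives a different split: "The control phase of the study included 11 months (January 2020 to November 2020") and "evaluation over the subsequent 37 months (December 2020 to December 2023"). The Abstract and the legend of Fig. 2 also give 11 and 37 months.

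**The concern.** The effect size, the underlying trend, the segment lengths and the end rate should describe one straight-line scenario, so any one of them can be checked from the others. Here they do not agree. The word 'difference' makes 0.57 and 0.44 look like the target value of the primary estimand, while the end rates imply a smaller target.

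This matters mainly for interpretation. Someone who reads the final estimate and its confidence interval against a planned change of 0.57 or 0.44 %/month would use too large a benchmark if the planned change was 0.47 or 0.39. In addition, the power statement refers to a 9+39 split that the trial does not have, and precision for a slope change depends strongly on the length of the shorter segment.

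**Working it through.** **Inputs (Sample size section).** Baseline b = 20% (treatment) and 10% (control). Underlying trend u = 0.10 and 0.05 %/month. Stated slope s = 0.57 and 0.44 %/month. Baseline months n0 = 9, intervention months n1 = 39. Stated month-48 rates: 42.5% and 27.0%.

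**Step 1: the label as worded (s is the change in slope).** End rate = b + u(n0 + n1) + s·n1.
- Treatment: 20 + 48×0.10 + 39×0.57 = 20 + 4.80 + 22.23 = 47.03%, against 42.5% stated (4.5 points too high).
- Control: 10 + 48×0.05 + 39×0.44 = 10 + 2.40 + 17.16 = 29.56%, against 27.0% stated (2.6 points too high).
- Rounding of the slopes (±0.005) gives ranges of 46.8 to 47.2% and 29.4 to 29.8%, so it cannot close the gap.
- Solving for the number of intervention months that would give the stated rates: (42.5 − 24.8)/0.57 = 31.1 and (27.0 − 12.4)/0.44 = 33.2. These match neither each other nor 39 or 37.

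**Step 2: s as the total intervention-phase slope.** End rate = b + u·n0 + s·k, where k is the number of monthly steps after the switch.

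| | k = 39 | k = 38 | Stated |
|---|---|---|---|
| Treatment | 20 + 0.90 + 22.23 = 43.13% | 20 + 0.90 + 21.66 = 42.56% | 42.5% |
| Control | 10 + 0.45 + 17.16 = 27.61% | 10 + 0.45 + 16.72 = 27.17% | 27.0% |

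With 39 steps the result is still 0.6 points high for both outcomes. With 38 steps (month 10 to month 48), back-solving the stated rates gives (42.5 − 20.9)/38 = 0.568 and (27.0 − 10.45)/38 = 0.436, which round to the printed 0.57 and 0.44. The 38-step count is an inference; the article does not state it.

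**Step 3: implied change in slope.** Treatment: 0.57 − 0.10 = 0.47, which is 0.10/0.57 = 18% below the label. Control: 0.44 − 0.05 = 0.39, which is 0.05/0.44 = 11% below.

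**Step 4: the actual 11+37 split, total-slope reading.**
- 37 steps: 20 + 1.10 + 21.09 = 42.2%; 10 + 0.55 + 16.28 = 26.8%.
- 36 steps (the same one-fewer convention that fits Step 2): 20 + 1.10 + 20.52 = 41.6%; 10 + 0.55 + 15.84 = 26.4%.

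**Step 5: does the split matter for precision?** In segmented least squares with a level term, the standard error of the slope change per unit residual SD is 0.130 for 9+39 and 0.097 for 11+37, about 26% lower. Without a level term it is 0.094 and 0.074, about 21% lower.

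**Step 6: illustrative power.** Assumptions, not figures from the article: 1200 visits per month, binomial noise only, independent months, ordinary least squares, two-sided 5%, 20,000 simulated trials.

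| Split and model | Treatment, change 0.47 | Control, change 0.39 |
|---|---|---|
| 9+39, with level term | 79% | 81% |
| 9+39, without level term | 97% | 98% |
| 11+37, either model | at least 97% | at least 97% |

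Replacing the least-squares standard error with one that allows for the unequal binomial variances moves the first row to 86% and 92%. An assumed design effect of 2 then lowers it to 57% and 66%. The article does not give the inputs needed to choose among these.

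**The case against.** The strongest reply is that this is loose wording, not a wrong calculation. The sentence sets two slopes side by side, the end rates show which was meant, and a reader can subtract to get 0.47 and 0.39. The estimand is defined elsewhere without either number, so no analysis changes. Most of this stands: nothing in estimand, model or conduct is affected. It does not rescue the sentence, however, because it concedes that the change in slope is never stated and that 'difference' is the wrong word for the numbers printed.

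A reader might go further and infer that the trial is underpowered, or that the 80% claim has no margin. The documents do not support that. The 79% and 81% figures require a level-change term, whereas the Primary outcomes section speaks only of a change in slope and the Discussion of a linear slope change effect. Without that term, power under the same assumptions is 97% and 98%. Scenarios with extra month-to-month variation, autocorrelation or a much higher baseline treatment rate rest on values the article does not contain, and the variance inputs may properly sit in the full protocol or analysis plan.

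Nor is the 9+39 split evidence of lost power, since two more control months tighten the slope-change estimate. The allowance for 10 sites dropping out is conservative now that the Discussion reports the risk did not materialise, and literature base rates are ordinary planning inputs. Neither is an error.

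**Conclusion.** The point holds as an internal inconsistency in the Sample size section. As labelled, the slopes overshoot the section's own end rates by 4.5 points (treatment) and 2.6 points (control). Only the total-slope reading comes close, and it matches within slope rounding if 38 monthly steps are counted after the switch. On that reading the planned changes in slope are about 0.47 and 0.39 %/month. This rests on straight-line accumulation from 20% and 10%. Only the sponsor's simulation code can settle which quantity was entered.

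Separately, the section describes 9+39 months and the trial is 11+37, and the article does not reconcile the two. The claim of more than 80% power is neither confirmed nor refuted, and the change of split probably raises power.

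**What to change.** In the Sample size section:

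1. Check the simulation code and state whether 0.57 and 0.44 are total intervention-phase slopes or changes in slope. If total slopes, replace the word 'difference' and give the changes as about 0.47 and 0.39 %/month. If they are changes, correct the end rates instead.
2. Re-run the existing simulation for 11 control and 37 intervention months, and restate power for the change in slope. If the 9+39 figures are kept as the record of planning, say so.
3. Give month-48 rates under one explicit step convention. On the total-slope reading these are about 42.2% and 26.8% with 37 steps, or 41.6% and 26.4% with 36.

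The 50-site allowance and the literature base rates need no change. The cost is a re-run of existing code and one corrected paragraph, with no effect on conduct, estimand or analysis. It is best done before the primary results are interpreted against the planned effect.

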### Data quality assurance and control

To ensure data quality, we built in field validation(s) and branching logic within the REDCap forms. Before obtaining data entry rights, all study team members and healthcare workers with data access privileges completed training and pilot tested data entry using hypothetical data. Centralized statistical monitoring are performed through weekly data and status quality reports. The data and status quality reports use the REDCap application programming interface functionality to export the program data, and then are restructured and summarized using statistical software packages, including R (v4.0.3, R Core Team, Vienna, Austria) and SAS (v9.4, SAS Inc., Cary, NC). The reports are reviewed and discussed bi-weekly. Because the systems are in place and code has been generated, the reports can be updated in real time.

### Statistical analyses

All participants who are enrolled in the patient registry will be accounted for, in accordance with the consolidated standards for reporting trials (CONSORT) statement for transparent reporting of trials (Fig. 3; Additional file 6). As of May 2022, more than 16,000 individuals participated in the Program. Baseline demographic variables, such as age, sex, and relevant clinical variables will be summarized when results are reported. Summaries of continuous baseline variables will be presented as means and standard deviations or medians with minimum and maximum values as appropriate and based on distribution. Categorical variables will be described as frequencies and percentages.

**Fig 3 Fig3:**
[figure not shown]
CONSORT Flowchart of Enrollment, Eligibility, and Analytic Sample Size in the Hypertension Treatment in Nigeria Program from January 1, 2020, through May 5, 2022

The statistical analysis will be performed using the intention to treat principle (i.e., all patient visits recorded in the database will be included and considered exposed to the intervention or unexposed according to the overall program timeline, regardless of when the intervention was actually implemented). The statistical design of the program intervention includes evaluation of effectiveness and implementation co-primary outcomes, which is consistent with the type 2 hybrid design. For implementation outcomes, we will use quantitative and qualitative analysis using the RE-AIM framework to triangulate routinely collected data to evaluate the reach, secondary effectiveness, adoption, implementation, maintenance, acceptability, and cost of the implementation package [12]. We will seek to explore and explain variability across key subgroups, including age, sex, and geography.

For effectiveness outcomes, we will use an interrupted time series evaluation with aggregate measures of system-level monthly treatment and control rates to evaluate temporal trends. We will evaluate change in temporal trends for primary and secondary outcomes through segmented linear regression by aggregating data across primary healthcare centers by month. To evaluate effects of each implementation package component and time variance in implementation on our primary outcomes, we will use patient-level mixed-effects models including random effects to account for clustering at the primary healthcare center level. We will perform sensitivity analyses by both excluding and restricting repeated measures of the same patients over the program period.

For the home blood pressure and health coaching sub-study, we will use analysis of covariance, controlling for baseline clinic-measured systolic blood pressure and medication to estimate the effect of a community health extension worker-led health coaching and home blood pressure monitoring on a 12-week change in systolic blood pressure compared with propensity-matched patients in the participating sites as controls. For implementation outcomes, we will adapt the RE-AIM framework and use quantitative data to evaluate the reach, effectiveness, adoption, implementation, maintenance, and cost of the interventions.

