### Intervention

The implementation package components were informed by the KPNC intervention toolkit and WHO HEARTS technical package (Fig. 1). To adapt the implementation package, we performed formative in-depth interviews and focus group discussions with patients, healthcare workers, and administrative staff to identify facilitators, barriers, and context to implementation of hypertension services within primary healthcare centers in the Federal Capital Territory, Nigeria [17]. The final implementation package includes a hypertension patient registry (health system level), performance and quality reporting (health clinic level), simplified treatment guidelines (national policy level), fixed-dose combination therapy (health system level), access to essential medicines and technology (health system level), team-based care and non-physician follow-up (health worker level), and health coaching and home blood pressure monitoring (patient level), all of which have demonstrated improved population-level hypertension control in other settings (Table 1) [3, 22, 23].

**Table 1 Tab1:** Hypertension Treatment in Nigeria Program implementation package

Component	Start date	Number of sites	Level of intervention	Description as used in the HTN Program	Evaluation
Hypertension Patient Registry and Empanelment	January 2020	60	Health System	Paper-based registration and case report forms facilitate site-based tracking and follow-up of patients, aligns with existing practices for health record management, and are easy to implement. The electronic database facilitates rapid roll up of information in a structured database with built-in quality assurance checks.	Supportive supervision visits include comparison of the site visit logs and the hypertension registry to evaluate completeness of the registry. Bi-weekly data and safety quality reports are generated to review electronic data. Central and on-site training and reinforcement are provided, including the latter during site supervision visits to register all adult hypertensive patients.

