Performance and Quality Reporting	December 2020	60	Health Clinic	Monthly performance and quality reports are issued to each participating site to summarize key metrics, aggregated over a rolling 3-month period. Metrics include treatment, control, and retention rates, along with lists of patients for targeted follow-up. Comparisons are made with other sites in the HTN Program.	Data quality audits are conducted during supportive supervision visits to compare data between the paper and electronic case report forms, and correct errant data points. Study team members communicate with sites on a quarterly basis to follow up on performance reports and ascertain if the site has reviewed and understood the report. In interim and final qualitative evaluations, sites will be asked for their feedback on the performance reports.
Simplified Treatment Guideline	December 2020	60	National Policy	A four-step simplified treatment guideline was enacted in the 2019 Nigeria Hypertension Protocol.	Medications data collected in the registry are used to calculate adherence to the four-step protocol by site, and across the program. In interim and final qualitative evaluations, sites will be asked for their feedback on the treatment guideline (appropriateness, feasibility, and adaptation).
Fixed-dose combination	December 2020	60	Health System	Fixed-dose combinations are encouraged in the hypertension treatment guideline when available.	Medications data collected in the registry are used to evaluate administration of fixed-dose or single pill prescriptions by site, and across the program. In interim and final qualitative evaluations, site will be asked for their feedback on fixed-dose combinations (appropriateness, feasibility, and adaptation).
Access to Essential Medicines and Technology	December 2020	60	Health System	Initial hypertension drug supplies were provided to all participating sites to prime the Drug Revolving Fund. During the first year of the intervention phase, work was completed to enact agreements for provision of hypertension medications at reasonable cost. The study team developed protocols, strategies, and training for adding hypertension medications to the Drug Revolving Fund.	Implementation of the Drug Revolving Fund will be evaluated in a separate protocol through RE-AIM outcomes. Early access to medicines in the study is evaluated through treatment rates, as well as stockout and replenishment rates at the participating sites.

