Team-Based Care and Community Health Extension Worker Provided Hypertension Management	December 2020	60	Health Worker	Frontline workers (CHEWs, CHOs, pharmacists) have been trained during the control and intervention phase on components of the intervention package. A multidisciplinary team is involved in providing hypertension services in the participating health clinics.	Implementation of team-based care is evaluated through site supervision visits and provider reported experience.
Health Coaching and Home BP Monitoring	September 2022	10	Patient	CHEWs will lead a home-based blood pressure monitoring and health coaching (using motivational interviewing approach) intervention.	Implementation and effectiveness of the home blood pressure monitoring arm will be evaluated through a separate protocol including evaluation of blood pressures and pre- and post-intervention questionnaires.

*Abbreviations*: *CHEW* Community health extension worker, *CHO* Community health officer, *HTN* Hypertension Treatment in Nigeria

During the first 11 months (January 2020 through November 2020) of the program, all sites were in the control phase of the program during which time the only implementation package component used was the paper- and electronic-based patient registry. At initiation of the control phase, a 2-day, in-person training was provided to a minimum of two CHEWs from each participating site, which was focused on measurement of blood pressure, diagnosis of hypertension, and record management (Additional file 5) [24]. Pre- and post-workshop tests were conducted to evaluate changes in knowledge and practice, including evaluation of accurate blood pressure measurement. Record officers at each site were also trained through an in-person half-day training on electronic data management.

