In December 2020, all sites transitioned to the intervention phase of the program. Healthcare workers participated in a full-day in-person training focused on a simplified treatment guideline following the Nigeria 2019 Hypertension Protocol, appropriate case management and patient treatment, and use of performance and quality reports [10]. The team trained six supervising Pharmacists/Pharmacy Technicians, one from each area council, and one pharmacy focal health worker from each of the 60 HTN primary healthcare centers on drug dispensing and logistics management before commencing the intervention phase. Primary healthcare center personnel were also retrained centrally at periodic intervals as well as quarterly, on-site supervision visits. Training was informed by feedback from audit and supervision reports. Moreover, all other full-time staff of the participating primary healthcare centers who were not among the healthcare workers initially selected for HTN Program were trained to build their capacity and to assist in the Program based on future needs. All training provided to staff at the participating primary healthcare centers was facilitated by supervisors who are members of the study team at University of Abuja Teaching Hospital.

In November 2021, a 2-day in-person training was provided to 30 CHEWs and 10 facility managers from 10 participating sites on how to carry out the home blood pressure and health coaching sub-study. The training focused on health coaching and motivational interviewing, screening consent at the participating sites, medication management, behavioral change related to hypertension, accurately measuring clinic and home blood pressure, health coaching visits, and role-playing. Pre-and post-training tests were conducted with CHEWs to understand changes in current knowledge and experience in health coaching and blood pressure monitoring. A second training session in April 2022 served as a refresher.

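### Effects of each package component are promised, but on the program calendar the five December 2020 components can only be estimated jointly and the registry not at all

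*Protocol article*

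**What the plan says.** The Statistical analyses section of the protocol article sets out two layers of effectiveness analysis. The co-primary outcomes are analysed by segmented linear regression of program-wide monthly rates. A second analysis then goes below the bundle: "To evaluate effects of each implementation package component and time variance in implementation on our primary outcomes, we will use patient-level mixed-effects models", with random effects for clustering by center.

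The same section opens with an exposure rule. Visits are "considered exposed to the intervention or unexposed according to the overall program timeline, regardless of when the intervention was actually implemented". No exception is made for the mixed models.

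The rollout is described under Intervention. In the control phase "the only implementation package component used was the paper- and electronic-based patient registry". Then: "In December 2020, all sites transitioned to the intervention phase of the program". Table 1 gives start dates and site counts, among them "Hypertension Patient Registry and Empanelment January 2020 60", "Performance and Quality Reporting December 2020 60", "Simplified Treatment Guideline December 2020 60" and "Fixed-dose combination December 2020 60". Access to medicines and team-based care carry the same December 2020 date and 60 sites. Health coaching with home blood pressure monitoring is dated September 2022, in 10 sites.

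**The concern.** Separate effects need separate contrasts: for each component there must be visits with it and visits without it that differ in some way other than through the remaining components. Table 1 supplies such a contrast for one component out of seven. Five switch on together everywhere, and the registry is never off.

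If the models were fitted with calendar indicators, the software would drop redundant columns or fail to converge, and the surviving coefficients would depend on which columns were kept. A ranking of components from such output would be an artefact. This matters because the article presents the trial as evidence for wider scale-up, where a reader will naturally ask which parts of the package are worth keeping.

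**Working it through.** The plan states no figure on this point, so the check is of identifiability: build the exposure columns from Table 1 and take the rank.

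**Inputs.** The Timeline section gives 11 control plus 37 intervention months, so 48 months. Counting January 2020 as month 1, December 2020 is month 12 and September 2022 is month 33. With 60 sites there are 60 × 48 = 2,880 site-months.

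| Component | Start | Sites | Column |
|---|---|---|---|
| Registry | month 1 | 60 | 1 throughout |
| Performance reporting | month 12 | 60 | P |
| Simplified guideline | month 12 | 60 | P |
| Fixed-dose combination | month 12 | 60 | P |
| Access to medicines | month 12 | 60 | P |
| Team-based care | month 12 | 60 | P |
| Coaching and home monitoring | month 33 | 10 | H |

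Here P = 1 from month 12 in every site, and H = 1 from month 33 in the 10 coaching sites.

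**Level model.** With month t:

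b0 + b1·t + g1·1 + (g2 + g3 + g4 + g5 + g6)·P + g7·H
= (b0 + g1) + b1·t + (g2 + … + g6)·P + g7·H

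The data determine four quantities: b0 + g1, b1, the sum g2 + … + g6, and g7. That is rank 4 of 9 columns. Intercept and trend account for 2, so the seven components add 4 − 2 = 2.

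**With slopes.** Five component-specific terms of the form P·(t − 11) make 9 + 5 = 14 columns, but they are one column repeated, so the rank is 5. A slope for coaching as well gives 15 columns and rank 6.

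**With site and calendar-month fixed effects.** P is absorbed by the month effects and the registry by the intercept. Only coaching adds rank: 1 of 7.

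**Patient level and random effects.** A patient-visit row repeats the P and registry values of its site-month, so moving to patient level adds rows but no contrast for these six components. Coaching reaches selected patients only, but remains one separable column. Center random effects change the covariance structure; they cannot split P, because P does not differ between centers.

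**If actual start dates were used instead.** The article gives no site-level lags. As an assumption, let each of the five components start in each site with an independent lag of 0 to L months (one random draw per L):

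| L (months) | Rank added, of 7 | Variance inflation, five components | Factor on standard error (square root) |
|---|---|---|---|
| 0 (as in Table 1) | 2 | infinite | – |
| 1 | 6 | 26.1 to 32.2 | 5.1 to 5.7 |
| 3 | 6 | 10.7 to 14.1 | 3.3 to 3.8 |
| 6 | 6 | 7.1 to 8.0 | 2.7 to 2.8 |
| 12 | 6 | 4.3 to 4.8 | 2.1 to 2.2 |

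The rank added is 6 and not 7 at every non-zero lag because the registry stays aliased with the intercept. Independent lags are a favourable assumption: components that start together within a site would be more collinear.

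**The case against.** The strongest reply is that the rank figures rest on a coding the article does not state. The sentence that promises component effects also names time variance in implementation, which suggests exposure measured by delivery. The article does describe delivery that can vary. Table 1 lists fixed-dose prescribing and adherence to the four-step protocol by site, and stockout and replenishment rates. Table 3 lists monthly center-level proportions for stepped care and fixed-dose use. Medicine supply arrangements were completed during the first intervention year. Variable definitions can also fairly be left to an analysis plan that is not shown.

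Much of this stands. A reader might infer that no component effect can be estimated, or that the mixed models must fail. The document supports neither inference. Coaching differs in time and place and has its own analysis of covariance against propensity-matched controls. A delivery-based model for the five common components could be fitted. Nor is the main result in doubt: the mixed models are additional to the co-primary segmented regression.

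Three things remain. No analysis plan can supply registry-off data. A delivery-based model contradicts the calendar exposure rule, which is stated for the analysis as a whole. And delivery was not assigned by design, so sites that delivered more may differ in staffing, caseload or security; the coefficients are confounded associations. For the treatment-rate outcome there is also overlap: a patient on a fixed-dose combination is treated by definition, and Table 1 judges early medicine access partly by the treatment rate itself.

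**Conclusion.** The concern holds in limited form. Under the program-timeline rule, six of the seven components have no separately estimable effect: five are identified only as a sum, and the registry is not identified. The registry conclusion holds under any coding, because the article describes no registry-off data. The conclusion for the other five, and the ranks of 4 of 9 and 5 of 14, hold for calendar coding only. With actual delivery dates, separate associations become estimable. Their precision depends on site lags that the article does not give, and they would not be effects of introducing a component.

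The promise of an effect for each component therefore exceeds what the design can deliver, and the calendar rule and the reference to time variance in implementation need to be reconciled. The estimate of the package as a whole is not affected.

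**What to change.** 1. State that the interrupted time series estimates the effect of the December 2020 bundle over registry-only care, and remove the claim to effects of each component. Leave coaching to its own sub-study analysis.
2. Replace the claim with an exploratory analysis, labelled as association only, within the intervention phase and adjusted for center and calendar time. Exempt it explicitly from the program-timeline exposure rule.
3. Restrict it to measures actually recorded by site and month: the monthly stepped-care and fixed-dose-combination proportions, and stockout records where they exist at that frequency. Several fidelity measures do not qualify. In Table 3, medicine availability is taken on the day of assessment and supervision is counted over seven months. Monitoring visits are quarterly to six-monthly. Performance reports go to every site each month, so receipt may hardly vary.
4. Do not use fixed-dose use or drug availability to explain the treatment rate without stating their overlap with it.

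The cost is a change of wording, a check of which delivery records exist by site and month, and one exploratory model. The price in interpretation is a weaker statement about components. The co-primary analysis needs no change.
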